### Gait speed

The participants will be instructed to walk at a normal speed on a 6-m-long corridor without a barrier, and the usual gait speed is calculated by measuring the time spent to reach the end of the corridor by a participant as suggested by the AWGS (52). The participants could walk with or without assistive devices during the measurement. The time will be initially recorded once the participants start walking and stop at the point when they reach a distance of 6 m. Gait speed should be measured two times, and the average of the two speeds will be recorded. The participants will be allowed to rest for 10 min between measurements. The MCID of gait speed across multiple patient groups is 0.10–0.20 m/s (56).

### Study of osteoporotic fractures index

The SOF index consists of the following three components: (a) a weight loss of ≥5% during the preceding year (regardless of the intention to lose weight), (b) the inability to rise from a chair five times without using the arms, and (c) an answer of “no” to the question “Do you feel full of energy?” The participants will be identified to be frail if they have two or more of the aforementioned components; those with one disability are considered in pre-frailty status, and those with none of the aforementioned impairments are considered robust (57). The SOF index has been proven to be a valid tool to evaluate frailty, particularly for community-dwelling older adults in Taiwan (58).

## Secondary outcomes

### Manual dexterity

The box and block test (BBT) can be used to measure the unilateral gross manual dexterity in various populations with high test–retest reliability and validity (59). The setup of the BBT consists of a wooden box divided into two compartments, with 100 wooden blocks inside one compartment. The participants will be instructed to transfer the wooden blocks one by one from one compartment to the other in the sitting position. The score is based on the number of blocks the participants transferred in 60 s. Most studies on the MCID of the BBT have involved patients with stroke, and the MCID was 5.5 cubes/min for the most affected side and 7.8 cubes/min for the least affected side (60).

### Biceps and triceps brachii muscle strength of the dominant side

We will use the microFET^®^ 3 (Hoggan Health Industries, West Jordan, UT, USA) to measure the maximal voluntary isometric contraction (MVIC) of the biceps and triceps brachii of the dominant side. The microFET^®^ 3 is an electronic handheld dynamometer that can detect 0–150 lb of force with high reliability and validity (61). The participants will be instructed to lie on the treatment table with their elbows forming a 90° angle to the horizontal such that the arm is perpendicular to the limb. The device will be placed on the ventral (for the biceps brachii) or dorsal (for the triceps brachii) side of the arm and aligned with the ulnar styloid. The participants will be encouraged to go against the force, which is exerted toward the device, with their maximum strength (62). The MVIC will be measured two times, and the average of the two measurements is recorded. The participants will be allowed to rest for 1 min between measurements.

### Sonographic thickness of biceps and triceps brachii muscles

A single-experienced operator, who is not involved in any further data analysis and is blinded to clinical symptoms, will use a portable LOGIQ e-ultrasound (General Electric Company, USA, 2010) equipped with a 5–12-MHz linear array transducer to measure the muscle thickness under sonography. Measurements should be performed by gently applying the transducer onto the skin that is coated by a thin layer of water-soluble gel. The transducer should be held orthogonal to the skin surface to ensure precise depth analyses and avoid transmission parallax error. All participants will undergo measurements in the afternoon. All measurements will be performed once on each side and recorded, respectively. The position used to measure each muscle is as follows:

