### Dominant hand grip strength

The HGS will be measured using a JAMAR dynamometer (J A Preston Corporation, New York, NY, USA) using all five notches. A JAMAR dynamometer is a hydraulic instrument that measures isometric strength in kilograms. It has been proven to have good reliability in various older populations (53). The measurement will be performed under a standard position, and the instrument should be freely held. Each participant will be instructed to sit straight with their upper arm in a neutral position and their elbow flexed at 90°C, their forearm in a neutral position, and their wrist at 0–30°C extension (54). The measurement should be performed three times, and the highest of the three measurements will be recorded. The participants will be allowed to rest for 1 min between measurements. The minimal clinically important difference (MCID), defined as the minimal amount of change required to distinguish a true performance change due to variability in performance or measurement error, is also measured in this study. No available studies on the MCID of the HGS in older adults so far, whereas, in healthy individuals, the MCID of the HGS is 2.44–2.69 kg (55).

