Another feature of using RFA to deliver exergames is that it could set up the initial amount of exercise that must be performed in each stage and adjust it progressively and automatically depending on the performance of the player. Therefore, the progression for the exercise prescription might be individualized, and it is time- and manpower-saving given that it could be modified by the machine. The ACSM suggests increasing intensity over time to maintain the intensity of the exercises at moderate levels (41–60% of 1 RM for resistance exercise and Borg RPE 12–14 for aerobic exercise) (76). Therefore, the study protocol sets the target intensity of the exergame-based exercise at Borg RPE 13 and leaves the weight intensity to Nintendo Switch itself. Although it is practical to do so in real-world settings, and it is safer for the elderly to perform PRT by squeezing or stretching the Ring-Con, one limitation is that we cannot confirm whether the weight intensity given by the Ring-Con is sufficient at moderate levels.

Given that many elderly individuals in LTCFs use a wheelchair for community ambulation because of poor muscle endurance even though they can walk for a short distance to complete gait measurements (40), the exergame-based exercise of this project focuses on training the upper extremities and trunk. By doing so, the participants could be trained in the sitting position to avoid the potential risk of falls. Therefore, most outcomes of this project, including the HGS, MVIC, sonographic thickness of the biceps and triceps brachii muscles, ROMs of the joints of the dominant upper extremity, and BBT, are measured to evaluate the training effects. A study has proven that aging can attenuate the hypertrophic response of muscle groups to RT (77). Contrary to the findings from healthy young adults, in whom neural factors account for a larger proportion of the initial strength increment and muscle hypertrophy becomes the dominant factor after the first 3–5 weeks (78), the effect of muscle training may entirely depend on the neuromuscular adaptation among older adults after an 8-week training course (79). Given the results from the classical studies by Moritani and deVries and considering that the project lasted only 3 months, we measured not only the MVIC but also the sonographic thickness to see whether some early morphological changes in the trained muscles could be detected earlier.

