Supervised exercise is safe for frail older adults (85). Only one well-trained assistant will be required to supervise the entire exergame-based exercise procedure in this project. Many participants can play the game simultaneously if the number of Nintendo Switch and RFA is sufficient, which is time- and manpower-consuming. However, this study protocol has some limitations. First, this study used the convenience sampling method because recruiting older adults who regularly participate in LTCFs publicly is difficult and impractical. This project might be less representative, even though the minimum estimated sample size can be met. The results of this study should be applied with caution and could only be generalizable to similar populations. Second, the exergame-based exercise and outcome measures only lasted 3 months. This duration might be insufficient to observe an increase in the muscle mass of older patients. However, given that an intervention period of more than 3 months might lead to a higher attrition rate of the participants, particularly for those in LTCFs with several comorbidities, we will also measure muscle morphology using sonography to detect any earlier change in muscle parameters, and we still suggest a 3-month protocol. Third, to our knowledge, this project is the first study to evaluate the effectiveness of using RFA among elderly individuals living in LTCFs. No established protocol for training with RFA could be followed. Although the entire exercise prescription is based on the guidelines for older adults by the ACSM, we cannot ensure that the protocol for the current exergame-based exercise is ideal. Fourth, individualized setting and progression of the exercises automatically are the features of using RFA to train elderly individuals. However, this project can only measure the exercise intensity by RPE. The investigators cannot confirm the exact resistance provided by the Ring-Con during each training session.

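### Muscle thickness is read from one ultrasound image per muscle and side; averaging two or three repositioned images would sharpen this secondary outcome at small cost

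*Protocol article*

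**What the plan says.** The section on sonographic thickness fixes the number of readings: "All measurements will be performed once on each side and recorded, respectively". It also sets safeguards. One experienced operator does every scan, scans take place in the afternoon, and the transducer is applied gently and at right angles to the skin. The biceps and triceps subsections add bony or skin landmarks, limb position, scan plane and minimal pressure.

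Repeat readings are specified for some other outcomes:

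- Isometric strength of biceps and triceps: "The MVIC will be measured two times, and the average of the two measurements is recorded".
- Gait speed: "Gait speed should be measured two times, and the average of the two speeds will be recorded".
- Grip: "The measurement should be performed three times, and the highest of the three measurements will be recorded".

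The discussion gives thickness a particular task. The authors measure strength and "also the sonographic thickness to see whether some early morphological changes in the trained muscles could be detected earlier". Among the limitations they say of the three-month programme: "This duration might be insufficient to observe an increase in the muscle mass of older patients". They then add: "we will also measure muscle morphology using sonography to detect any earlier change in muscle parameters".

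Reliability is cited for the grip dynamometer, the box and block test and the handheld dynamometer. None is given for ultrasound thickness.

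**The concern.** Thickness is meant to show change that may be too early or too small to appear in muscle mass. The discussion itself notes that ageing can blunt hypertrophy and that short-term gains may be wholly neuromuscular. A single image carries the operator's placement, pressure and caliper error in full, at baseline and again at follow-up, and both errors enter the change. The closest comparator is isometric strength: same muscles, adjacent section, two averaged readings. The article gives no reason for the difference.

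What is at stake is precision. Random reading error in both arms widens the interval around the group difference, so a real early change could be missed. Baseline repeats cannot be recovered later.

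**Working it through.** The plan states no power, effect size or reliability for thickness, so it has no figure of its own to reproduce on this point. Only the group size is borrowed from its sample size section. That section gives 18 per group, sized on the muscle mass index with f = 0.4, alpha 5% and power 80%. The figure can be recovered with a repeated-measures between-group F test at three visits, if a correlation of 0.5 is assumed (the article states none): lambda = 0.4² × 36 × 3 / (1 + 2 × 0.5) = 8.64, power 81.5%.

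**Error reduction.** If k images are taken with independent errors and averaged, the error SD is multiplied by 1/√k.

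- k = 2: 1/√2 = 0.71, a cut of 29%.
- k = 3: 1/√3 = 0.58, a cut of 42%.

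**Effect on the group comparison.** Work in units of the SD of one reading, with R the reliability of a single reading. The variance of a change between two visits is

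v = (true-change SD)² + 2(1 − R)/k.

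Approximate power for a difference δ in mean change with n per group is Φ(δ / √(2v/n) − 1.96).

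Assumptions, none given in the documents: δ = 0.2, true-change SD = 0.2, and R from 0.80 to 0.99. From the plan: n = 18.

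Example at R = 0.90:

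- k = 1: v = 0.04 + 0.20 = 0.24, SD 0.490; 0.2 / (0.490 × √(2/18)) = 1.22; power = Φ(−0.74) = 23%.
- k = 2: v = 0.04 + 0.10 = 0.14, SD 0.374; ratio 1.60; power 36%.
- k = 3: v = 0.04 + 0.067 = 0.107, SD 0.327; ratio 1.84; power 45%.

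| Assumed R | 1 image | 2 images | 3 images |
|---|---|---|---|
| 0.80 | 15% | 23% | 30% |
| 0.90 | 23% | 36% | 45% |
| 0.95 | 36% | 52% | 60% |
| 0.99 | 69% | 77% | 79% |

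Two images instead of one add about 8 to 15 percentage points across this range. If 40% of the planned 26 per group left, 26 × 0.60 = 15.6 would remain, and every entry would be somewhat lower.

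**When the gain shrinks.** Let s be the share of error variance common to all images of one visit (hydration, for example). The error SD is then multiplied by √(s + (1 − s)/k). With s = 0 this gives the cuts above; with s = 1 repeat images gain nothing. The table assumes s = 0 and so shows the most that repeats could achieve.

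**The case against.** The strongest reply is that nothing here is misstated or contradictory, and that the article already controls the main error sources. Thickness is a passive image read by one trained operator, whereas gait speed and strength are performed by the participant and vary with effort, so the numbers of repeats are not like for like. No repeats are stated for the muscle mass index, the box and block test or range of motion either. Grip keeps the highest of three trials, which is not averaging. Much of this stands: the comparison with other outcomes is only suggestive, and grip should not be counted in it. But the safeguards reduce one operator's residual error without averaging it, and that is the part repeat images address.

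Both sides are scanned, and the training uses both arms. Left and right are different muscles, not replicates of one site, but a two-side mean would already recover some precision for a group-level effect. That also stands, and it tells against confining the analysis to the dominant side merely because strength is measured there.

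A reader might infer three stronger claims that the article does not support:

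- That ultrasound is the justification for the 12-week duration. The stated reason for not going beyond three months is attrition; sonography is an added measure.
- That thickness is the least precise measure, or has the smallest expected change. No reliability or expected change is given for it, and the number of readings is not precision.
- That the single reading biases the result. Outcome assessors are blinded, so the error should fall on both arms alike.

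**Conclusion.** The point holds as an inexpensive improvement to one secondary outcome. A single image per muscle and side leaves within-operator error unaveraged in the measure the authors look to for early morphological change. The proportional cut in error SD, 29% with two images and 42% with three, depends only on the errors being independent within a visit. The power figures rest further on an assumed reliability, effect and true-change SD. At low reliability repeats help but do not rescue the comparison (15% to 30%); at very high reliability the gain is modest (69% to 79%). The primary analysis is unaffected.

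**What to change.** In the sonographic thickness section, replace the single reading with two (or three) images per muscle and side by the same operator, with the probe lifted and repositioned between images, and analyse their mean. Keep both sides and the existing safeguards. The repeats would also let the trial report its own within-operator reliability. The rule should apply from the baseline scan onward.

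The cost is operator time. Table 2 lists four muscles; if all are scanned on both sides, a visit rises from 4 × 2 = 8 images to 16 or 24, at three visits, for one operator working in the afternoons. If that is too much, repeat only the trained arm muscles, biceps and triceps. This adds 2 × 2 = 4 images per visit for a second reading, or 8 for a second and third. No extra staff or device is needed.

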#### Biceps brachii muscle

The thickness of the brachial biceps will be obtained at two-third of the way between the acromion and the antecubital crease of the examined upper limb with the transducer placed perpendicular while exerting minimum pressure. The examined upper limb should be extended fully. The thickness is measured in the transverse plane (63).

#### Triceps brachii muscle

The thickness of the brachial triceps will be obtained at the proximal one-third of the way between the acromion and the olecranon of the examined upper limb with the transducer placed perpendicular while exerting minimum pressure. The examined upper limb should be overhead and extended fully. The thickness is measured in the transverse plane (64).

### Measurement of the range of motion of the joints of the dominant upper extremity

The range of motions (ROMs) of the dominant upper extremity, including shoulder flexion, abduction, and external rotation; elbow flexion and extension; forearm supination and pronation; and wrist flexion and extension, will be measured. The ROMs will be measured using a goniometer under standard positions (65).

### General function

We will use the Kihon checklist-Taiwan (KC-T) to indicate the ADLs of the participants in this study. The KC-T is a self-reported questionnaire consisting of 25 items divided into seven subcategories: general independence, physical strength, nutrition, oral function, level of social activities outside the home, cognitive function, and risk of depression. Each item is rated as a pass (0) or fail (1); therefore, a higher total score indicates a lower level of function (66). The KC-T is used by the Ministry of Health and Welfare in Taiwan as an outcome indicator for community-based programs that delay and prevent disability (67), and its usability in practice in real-world settings in Taiwan has been proven (68).

### Health-related quality of life

We will use the Medical Outcomes Study 36-Item Short-Form Health Survey (SF-36) to indicate the HRQoL of the participants in this study. The SF-36 is a self-assessment validated generic health survey containing 36 items divided into eight subscales: physical functioning, role limitation due to physical problems, bodily pain, general health, vitality, social functioning, role limitation due to emotional problems, and mental health. The first four subscales represent the physical function, and the subsequent four subscales represent the mental function. Responses to each question will be transformed into a scale ranging from 0 to 100. The higher the scores, the better the HRQoL (69). All subscales have high levels of validity and reliability. The SF-36 has an acceptable internal consistency (Cronbach’s α value ranged from 0.74 to 0.95) among the Taiwanese population (70). We will record the scores of the entire questionnaire, physical function, and mental function in this study.

### Cognitive level

We will use the Brain Health Test (BHT)–brief cognitive test (BHT-Cog) to measure the cognitive level of the participants in this study. The BHT, developed by the Taiwan Dementia Society, is a simple dementia screening tool with high validity that can help primary care physicians identify patients with cognitive impairment among subjects with memory complaints or those at a high risk of dementia. It consists of risk factors and a brief cognitive test. The BHT-Cog includes orientation to time, immediate and delayed recall of five items, a categorical verbal fluency test (listing four-legged animals in 1 min), and the Clock Drawing Test (10:10) (71). The Ministry of Health and Welfare also uses the BHT in Taiwan as an outcome indicator for community-based programs that delay and prevent disability (67).

## Statistical analysis

### Sample size calculation

Since a high-quality study evaluating the effects of a similar intervention on muscle strength, physical activity, and function was unavailable when we wrote our protocol, we used previous results from one study using augmented reality (AR)-based exercise for one of our primary outcome measures (ASMMI) (72) for this power calculation. The effect size of a similar study for the AR-based intervention is high (0.71). Based on G*Power (version 3.1.9.2, for Windows), at least 18 observations in each group should be recruited by detecting a difference of 2 standard deviations (SD) of the ASMMI between the groups with a power of 80% and alpha of 5%, and the effect size is determined to be high (*F*-test family, 0.4) (73). To account for an expected dropout rate of 40%, given that most participants in the LTCFs have comorbidities, we decided to increase this number to a group size of 26. Thus, the aim will be to include at least 52 patients in the study.

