## Outcomes measured

All participants will be subjected to three evaluations. The first evaluation is at baseline (Time 0), which is before randomization. The second and third evaluations will be performed at the end of the 6^th^ (Time 1) and 12^th^ (Time 2) weeks after the intervention, respectively (Table 2).

**TABLE 2 T2:** Instruments and measures to be implemented for data collection.

Instrument or measure	Outcome	Description	Time point	References
Appendicular skeletal muscle mass index	Diagnostic criterion of sarcopenia. Primary outcome	Measured by bioelectrical impedance analysis. Defined as the appendicular skeletal muscle mass (Kg) divided by the height squared (m^2^)	T0, T1, T2	(49, 52)
Dominant handgrip strength	Diagnostic criterion of sarcopenia. Primary outcome	Measured by JAMAR dynamometer under standard position.	T0, T1, T2	(54)
Gait speed	Diagnostic criterion of sarcopenia. Primary outcome	The participants are asked to walk at a normal speed on a 6-m long corridor without a barrier and the usual gait speed calculated by measuring the time spent by a participant.	T0, T1, T2	(52)
Study of osteoporotic fracture index	Indicator of frailty. Primary outcome	Including three components: (a) a weight loss of ≥ 5% during the preceding year, (b) an inability to rise from a chair five times without using the arms, and (c) an answer of “no” to the question “Do you feel full of energy?”	T0, T1, T2	(57)
Box and block test	Indicator of hand dexterity. Secondary outcome	The number of blocks the participants transferred in 60 seconds from one compartment to the other compartment of the wooden box.	T0, T1, T2	(59)
Biceps and triceps brachii muscle strength of the dominant side	Indicator of muscle strength. Secondary outcome	Using the microFET^®^ 3 to measure the maximal voluntary isometric contraction under standard positions.	T0, T1, T2	(62)
Sonographic thickness of biceps and triceps brachii, quadriceps, and gastrocnemius muscles	Indicator of muscle morphology. Secondary outcome	Using a portable LOGIQ e ultrasound, equipped with a 5-12 MHz linear array transducer, to measure the muscle thickness under standard positions.	T0, T1, T2	(63, 64)
Range of motion of the joints of upper extremity	Indicator of functional movement. Secondary outcome	Using a goniometer under standard positions to measure shoulder flexion, abduction, and external rotation; elbow flexion and extension; forearm supination and pronation and wrist flexion and extension.	T0, T1, T2	(65)

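### The sample-size paragraph gives two irreconcilable effects for ASMMI (2 SD and f = 0.4) and a third without a metric, so 80% power is not established for any named effect, test and time point

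*Protocol article*

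**What the plan says.** Under "Sample size calculation", the protocol article bases the calculation on ASMMI, one of four primary outcomes, and cites an augmented-reality exercise study: "The effect size of a similar study for the AR-based intervention is high (0.71"). It then reports that G*Power gives at least 18 observations per group for "detecting a difference of 2 standard deviations (SD) of the ASMMI between the groups with a power of 80% and alpha of 5"%. The same sentence adds that "the effect size is determined to be high (*F*-test family, 0.4"). The paragraph does not name the G*Power test, the number of measurements, the correlation between visits or the metric of 0.71. The 18 is then raised to 26 per group for an expected 40% dropout.

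Under "Quantitative data", the analysis of training effects is a mixed ANOVA with time within subjects and intervention between subjects. Which term decides is not said. Under "Outcomes measured" there are three evaluations (T0, T1 at week 6, T2 at week 12), and "The first evaluation is at baseline (Time 0), which is before randomization".

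**The concern.** A power statement should let the reader say which difference, in which test, the trial can detect. Here one sentence offers two between-group differences for the same calculation, and the sentence before it offers a third number on an unknown scale. The reader cannot tell whether the trial is sized for 0.71, 0.8 or 2 SD.

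The second worry is the test. If 18 came from the group main effect of a three-visit repeated-measures ANOVA, the calculation assumes a difference that is present on average across all visits, including one taken before anyone is randomised. Expected separation at T0 is zero, so that term dilutes any training effect. What is at stake is how an ASMMI result is read: the paragraph presents the trial as having 80% power, and as written nobody can check for what.

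**Working it through.** **Inputs.** From "Sample size calculation": alpha 0.05, power 0.80, effects 0.71, 2 SD and f = 0.4, 18 per group (N = 36), 26 per group after inflation, 40% dropout. From "Outcomes measured": m = 3 visits, T0 before randomisation. Assumed, because the document gives none: the between-visit correlation rho, compound symmetry, and the shape of the effect over time.

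**1. Reproducing 18 per group.** Repeated-measures ANOVA, between-groups effect, noncentral F with df 1 and N − 2:

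lambda = f² · N · m / (1 + (m − 1) · rho)

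With f = 0.4, m = 3, rho = 0.5:
- N = 36: lambda = 0.16 × 36 × 3 / 2 = 8.64, power 0.815
- N = 34: lambda = 8.16, power 0.791

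So N = 36, or 18 per group, comes out exactly. Other routes come as close. The time-by-group interaction with rho = 0 and epsilon = 0.5 also gives N = 36. With the SPSS-type effect size the interaction needs N = 34 (power 0.831 at N = 36).

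**2. Putting the effects on one scale.** For two equal groups f = d/2.
- f = 0.4 is d = 0.8
- 2 SD is f = 1.0, and 1.0 / 0.4 = 2.5
- 0.71 as d is f = 0.355; 0.71 as f is d = 1.42

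**3. Simple two-group comparison**, noncentral t, two-sided 5%, 80% power:

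| Effect | n per group | Power at 18 per group |
|---|---|---|
| 2 SD | 6 | >0.999 |
| 0.8 SD (f = 0.4) | 26 | 0.645 |
| 0.71 as d | 33 | 0.544 |
| 0.71 as f (d = 1.42) | 9 | 0.985 |

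None of the four gives 18.

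**4. What the main effect does when T0 carries no difference.** Let d_j be the difference in SD units at visit j and d̄ its mean over the three visits, with n = 18 per group:

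- main effect: lambda = (n/2) · 3 · d̄² / (1 + 2·rho), df 1 and 34
- interaction: lambda = (n/2) · Σ(d_j − d̄)² / (1 − rho), df 2 and 68

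An average of 0.8 SD with zero at T0 requires 0.8 × 3/2 = 1.2 SD at week 12 if the full effect is present by T1, or 1.6 SD with linear build-up (0, 0.8, 1.6).

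Worked case, 0.71 SD at week 12, linear (0, 0.355, 0.71), rho 0.5. Main effect: lambda = 9 × 3 × 0.355² / 2 = 1.70, power 0.245. Interaction: lambda = 9 × 2 × 0.355² / 0.5 = 4.54, power 0.446.

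| Week-12 effect, shape | Main, rho 0.5 | Interaction, rho 0.5 | Interaction, rho 0.8 | Interaction, rho 0.9 |
|---|---|---|---|---|
| 0.71 SD, linear | 0.245 | 0.446 | 0.847 | 0.991 |
| 0.71 SD, full by T1 | 0.394 | 0.568 | 0.936 | 0.999 |
| 0.8 SD, linear | 0.298 | 0.546 | 0.924 | 0.998 |
| 0.8 SD, full by T1 | 0.478 | 0.678 | 0.977 | >0.999 |

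Higher correlation helps the interaction and hurts the main effect: for 0.8 SD, full by T1, main-effect power falls from 0.478 at rho 0.5 to 0.363 at rho 0.9.

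**5. Detectable difference with the evaluable numbers.** 26 × 0.6 = 15.6, so 15–16 per group. Unadjusted, the detectable difference at 80% power is about 1.06 SD (n = 15) or 1.02 SD (n = 16). A baseline-adjusted T2 comparison multiplies this by √(1 − rho²):
- rho 0.5: factor 0.866, 0.89–0.92 SD
- rho 0.7: factor 0.714, 0.73–0.76 SD
- rho 0.9: factor 0.436, 0.45–0.46 SD

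**The case against.** The best defence is that the planned analysis is a mixed ANOVA, that the interaction is the usual test of a training effect, and that its power at 18 per group can be ample. It passes 99% at a correlation of 0.9, and for 0.71 SD with full effect by T1 it reaches 0.80 at about 0.7. A literal 2 SD difference would be detected almost surely. This stands. A reader might infer that the claimed 80% power is absent, and the document does not support that: power falls on either side of 80% according to a correlation that is not given.

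A reader might also infer that 18 per group can come only from the main effect including T0. That is not supported either. The G*Power test is unnamed, and an interaction setting gives the same N = 36. The main-effect route is the most natural match to f = 0.4 and three visits, but it is an inference.

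Third, 0.71 is reported as another study's result and 0.4 is the planning value, so they need not be equal. Read as d, 0.71 (f = 0.355) is close to 0.4 and slightly smaller; read as f, it makes 0.4 conservative. The gap is therefore an unexplained choice on an unstated scale, not a contradiction, and it cannot be said that the plan assumes more than the cited study found.

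Finally, the discussion concedes of the three-month period that "This duration might be insufficient to observe an increase in the muscle mass of older patients". That is a disclosed limitation, with sonography added in response, and it does not bear on the arithmetic.

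None of this reconciles 2 SD with f = 0.4.

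**Conclusion.** The point holds in this form. The 2 SD and f = 0.4 figures cannot describe the same two-group difference (2.5-fold apart; 6 versus 26 per group), and 0.71 cannot be placed without its metric. This part needs no assumption beyond two equal groups, which the 1:1 allocation gives.

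The rest is conditional. If 18 came from the main effect over T0, T1 and T2, that test has about 25–48% power for 0.71–0.8 SD at week 12 with rho 0.5. If the interaction decides, power for 0.71 SD runs from about 45% (linear build-up, rho 0.5) to over 99% (rho 0.9). All of these assume compound symmetry, no difference at T0 and 18 evaluable per group. The supportable conclusion is that 80% power is not established for any named effect, test and time point.

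**What to change.** Rewrite the sample-size paragraph:

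- Remove the 2 SD wording.
- State whether 0.71 is a d or an f, and why the planning value differs from it.
- Give one effect in one metric, for ASMMI, at one time point.
- Name the G*Power test and the term that decides: the time-by-group interaction or a baseline-adjusted difference at T2, not the group main effect that includes T0.
- State the assumed correlation and show the detectable difference over a range. For example, for the baseline-adjusted T2 difference with 15–16 evaluable per group at 80% power: about 0.89–0.92 SD at rho 0.5, 0.73–0.76 SD at 0.7 and 0.45–0.46 SD at 0.9.
- Name the same deciding term in the "Quantitative data" section.

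The cost is one rewritten paragraph and one added sentence. No patients or visits are added. The stated power may become less favourable.

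### The 26 per group set to allow for 40% dropout leaves 15–16 per group, below the plan's own minimum of 18; keeping 18 at that dropout needs 30 per group

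*Protocol article*

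**What the plan says.** All the inputs stand in one paragraph of the protocol article, under Statistical analysis, Sample size calculation.

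- Minimum size: "at least 18 observations in each group should be recruited".
- Operating characteristics: "with a power of 80% and alpha of 5" per cent.
- Effect size entered in G*Power: "the effect size is determined to be high (*F*-test family, 0.4").
- Attrition: "To account for an expected dropout rate of 40" per cent.
- Response to that attrition: "given that most participants in the LTCFs have comorbidities, we decided to increase this number to a group size of 26", so at least 52 participants in total.

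The only reason given for moving from 18 to 26 is the expected dropout. The section prints no inflation formula. It also does not say which F-test was chosen, how many measurements were entered, or what correlation between them was assumed.

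**The concern.** A dropout rate is a share of those enrolled. The allowance should therefore leave the required number after that share has been removed. Here it does not: removing 40% of 26 leaves fewer than 18.

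The enrolment target is thus presented as protecting a minimum that, on the plan's own forecast, it misses. The stated 80% power is tied to that minimum. The authors take attrition seriously elsewhere: the limitations paragraph of the discussion gives the risk of higher attrition among residents with several comorbidities as a reason for keeping the study to three months. The same paragraph refers to the minimum estimated sample size being met, so readers are likely to rely on this figure.

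**Working it through.** **Inputs from the sample size section:** minimum 18 per group, dropout 40%, group size 26, total 52, f = 0.4, alpha 5%, power 80%. **From Outcomes measured:** three evaluations (baseline, week 6, week 12).

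**1. Reproducing the stated 26**
- Multiplying up: 18 × (1 + 0.40) = 25.2, rounded up to 26. This matches.
- Dividing by the retained share: 18/(1 − 0.40) = 30. This does not match.

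The printed figure is what multiplication would give. That this is how it was obtained is an inference.

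**2. What 26 delivers at 40% dropout**
- Per group: 26 × 0.6 = 15.6, so 15–16.
- In total: 52 × 0.6 = 31.2, against 36 needed.
- Shortfall: (18 − 15.6)/18 = 13%.
- Largest dropout that still leaves 18: 1 − 18/26 = 30.8%, or 8 of 26.
- Size that retains 18 at 40% dropout: 30 per group, 60 in total.

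Step 2 does not depend on how 26 was reached.

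**3. Effect on power**

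The article does not give the G*Power settings, so this step rests on assumptions: a repeated-measures between-factors F-test with 2 groups, m = 3 measurements, f = 0.4, two-group total N and correlation ρ. The noncentrality is λ = f²·N·m/(1 + (m − 1)ρ), with 1 and N − 2 degrees of freedom.

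With ρ = 0.5 and N = 36, λ = 0.16 × 36 × 3/2 = 8.64 and power is 81.5%. The smallest even N reaching 80% is 36, so this setting reproduces 18 per group. In the same setting:

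| Per group | N | λ | Power |
|---|---|---|---|
| 18 | 36 | 8.64 | 81.5% |
| 16 | 32 | 7.68 | 76.5% |
| 15 | 30 | 7.20 | 73.6% |

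The loss is about 5 to 8 percentage points.

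**4. Range over the unstated correlation**

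| ρ | Total N for 80% | Power at 16 per group | Power at 15 per group |
|---|---|---|---|
| 0.3 | 30 | 85.0% | 82.5% |
| 0.5 | 36 | 76.5% | 73.6% |
| 0.7 | 42 | 68.7% | 65.7% |
| 0.8 | 46 | 65.3% | 62.3% |

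Of these four, only ρ = 0.5 returns the plan's 18 per group. The other rows show how far the answer depends on a setting that is not printed.

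**The case against.** The arithmetic in step 2 has no good rebuttal: nothing elsewhere in the article changes it, and the paragraph is continuous text with nothing removed. The objections bear on what may be built on it.

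- **The formula is not printed.** A reader might infer that the authors demonstrably multiplied by 1.4. The document does not show that. A plain two-group comparison at f = 0.4 also reaches 80.7% power at 26 per group, so the match with 25.2 rounded up is suggestive only. This stands, but the shortfall does not rest on it.
- **The power setting is a back-fit.** The between-factors test and ρ = 0.5 are chosen because they return 18. If the calculation was for the group-by-time interaction, power at these sizes would be far higher, although that setting does not return 18 at f = 0.4 and ρ = 0.5 (it needs only N = 12). This stands: 74–77% is conditional, whereas missing the stated minimum of 18 is not.
- **A much larger power loss is tempting but not supported.** A simple two-sample t-test at d = 0.8 has only 56–59% power at 15–16 per group, and a reader might set this against the planned 80%. But that test has just 64.5% power at the full 18, so most of the gap comes from changing the test, not from dropout. It is also not the planned analysis, which is a mixed analysis of variance over time.
- **52 is a floor and 40% is a forecast.** Enrolment may exceed 52 and dropout may turn out lower. Both are true, but the sentence claims that 26 accounts for 40%, and it does not.

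**Conclusion.** The point holds as an internal contradiction in the sample size statement. At the plan's own 40% dropout, 26 per group leaves 15–16, below its own minimum of 18; 30 per group would be needed, and 26 covers at most 30.8% dropout. This part needs no assumption beyond reading dropout as a share of those enrolled.

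The consequence for power is less certain and probably modest. Under the assumed setting that reproduces 18 per group, power is about 74–77% instead of 81.5%. Over correlations from 0.3 to 0.8 it runs from about 85% down to 62%, but the ends of that range do not reproduce the plan's figure. The documents do not support saying that the trial is severely underpowered because of this step. They do support saying that the stated size does not deliver what is claimed for it.

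**What to change.** Restate the sentence in one of two ways:

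1. Keep 26 per group (52 in total) and state that this retains 18 per group only if dropout is at most about 30%.
2. Keep the 40% forecast and state that 15–16 per group are then expected, below the 18 needed for 80% power. Give the power recomputed in the G*Power setting actually used, with the test, number of measurements and correlation named.

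The figure of 74–77% should not be copied in unless that setting proves to be the one assumed here. Randomising 30 per group is a further option only if recruitment allows it; it would add 8 participants (60 instead of 52).

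The restatement costs one sentence and no extra participants. Its downside is that the stated tolerated dropout, or the stated power, becomes slightly less favourable.
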